# Establishing and evaluating physician-pharmacist collaborative clinics to manage patients with type 2 diabetes in primary hospitals in Hunan province: study protocol of a multi-site randomized controlled trial in the era of COVID-19 pandemic

**DOI:** 10.1186/s12913-022-07653-8

**Published:** 2022-03-04

**Keywords:** Diabetes, Pharmacist, Collaborative clinics, Rural area, RCT

## Abstract

**Background:**

The COVID-19 pandemic has exerted an unprecedented and universal impact on global health system, resulting in noticeable challenges in traditional chronic disease care, of which diabetes was reported to be most influenced by the reduction in healthcare resources in the pandemic. China has the world’s largest diabetes population, and current diabetes management in China is unsatisfactory, particularly in rural areas. Studies in developed countries have demonstrated that physician-pharmacist collaborative clinics are efficient and cost-effective for diabetes management, but little is known if this mode could be adapted in primary hospitals in China. The aim of this proposed study is to develop and evaluate physician-pharmacist collaborative clinics to manage type 2 diabetes mellitus (T2DM) in primary hospitals in Hunan province.

**Methods:**

A multi-site randomized controlled trial will be conducted to evaluate the effectiveness and cost-effectiveness of the physician-pharmacist collaborative clinics compared with usual care for Chinese patients with T2DM. Six primary hospitals will participate in the study, which will recruit 600 eligible patients. Patients in the intervention group will receive services from both physicians and pharmacists in the collaborative clinics, while the control group will receive usual care from physicians. Patients will be followed up at the 3rd, 6th, 9th and 12th month. Comparison between the two groups will be conducted by assessing the clinical parameters, process indicators and costs on diabetes. A satisfaction survey will also be carried out at the end of the study.

**Discussion:**

If effective, the physician-pharmacist collaborative clinics can be adapted and used in primary hospitals of China to improve glycemic control, enhance medication adherence, decrease incidence of complications and reduce patients’ dependence on physicians. Findings from the present study are meaningful for developing evidence-based diabetes care policy in rural China, especially in the COVID-19 pandemic era.

**Trial registration:**

Chinese Clinical Trial Registry, ChiCTR2000031839, Registered 12 April 2020.

## Background

Globally, as of January 21, 2022, the COVID-19 pandemic has infected over 340.54 million confirmed cases and killed more than 5.57 million people worldwide, reported to WHO [1]. Currently, the Omicron variant has been detected worldwide and will spread more easily than the original SARS-CoV-2 virus, which will increase the number of new COVID-19 cases exponentially. Experts postulated that this pandemic may persist for the next few years and may even recur seasonally.

The COVID-19 pandemic has resulted in an unprecedented global health crisis, challenging routine health systems’ ability to cope with the pandemic and disrupting current best practices for other disease management [2, 3]. In order to cope with the pandemic, countries across the world have transferred a large number of physicians and nurses to treat the confirmed cases, conduct nucleic acid tests and make COVID-19 vaccine shots, resulting in shortage of medical resources for other diseases treatment. Thus, many countries have to limit standard outpatient clinics and decrease inpatient capacity. The COVID-19 pandemic has placed a noticeable effect on patients with chronic diseases who require long-term care, of which diabetes was reported to be most influenced by the reduction in healthcare resources in the pandemic [4]. Besides the difficulties of shortage in medical staff and standard outpatient clinics, delayed care seeking, limited self-care practice, transportation inconveniency and unidentified adverse events all contributed to the major challenges of traditional diabetes care in the COVID-19 era [5].

With high-speed economic growth and lifestyle changes in the last two decades, China currently has the world’s largest diabetes population, which is still growing rapidly. The prevalence of diabetes in China was reported to be 0.67% in 1980 and increased to 11.9% in the latest published nationwide epidemic investigation in 2021 [6]. Diabetes has become a major cause of mortality in China, and about 1.27 million deaths was reported attributable to diabetes annually according to the estimates from IDF (International Diabetes Federation) Diabetes Atlas in 2013 [7]. Similar to other countries, the majority of patients with diabetes in China are type 2 diabetes mellitus (T2DM). The direct medical costs of type 2 diabetes and its complications in China were estimated to be 26.0 billion USD in 2007 and to be 47.2 billion USD in 2030 [8].

So far, the predominant care mode of diabetes management in China is the traditional physician-led mode. Physicians are responsible to diagnose, treat and educate patients. Present diabetes management in China is unsatisfactory, particularly in rural areas. As reported in a national investigation, patients with T2DM in urban areas of China, 43.1% were aware of their diagnosis, 38.4% were treated, and only 53.3% of the treated patients had adequate glycemic control. The rates in the rural regions were even lower, which were merely 29.1%, 25.2% and 42.3%, respectively [6].

In developed countries, numerous pharmacists have expanded their roles from medication dispensers to integrated members of interdisciplinary healthcare teams by providing the service of medication therapy management (MTM), which is defined as “a service or group of services that optimize therapeutic outcomes for individual patients” [9]. Those pharmacists, with their pharmacotherapeutic knowledge and patient centered training, are qualified and irreplaceable partners of physicians to educate and monitor patients on medication therapies, which ultimately improve disease management, medication adherence and overall health-related quality of life [10, 11]. Based on a comprehensive literature review, we found that diabetes management participated by pharmacists can significantly enhance glycemic control, improve concomitant disease management, delay the risks for complications and is cost-effective compared to usual care [12–17]. Those studies suggest that the mode of a physician-pharmacist collaborative clinic may be an alternative effective strategy to manage T2DM in China.

So far, the physician-pharmacist collaborative clinic is gaining recognition in some tertiary hospitals in China. However, to our knowledge, no collaborative clinics have been set up in primary hospitals in China yet, and one major reason is probably that the majority of pharmacists in primary hospitals are not confident or qualified to provide MTM services. According to China's hierarchical health care system, patients in primary hospitals usually have mild conditions with a few complications or comorbidities, and those with severe conditions are usually treated in tertiary hospitals. Therefore, if pharmacists could provide MTM services at the early stage of diabetes in primary hospitals in China, it may be very effective and promising to control and delay the progress of diabetes. However, little is known about the efficacy and cost-effectiveness of physician-pharmacist collaborative clinics for T2DM management in primary hospitals in China.

Therefore, we proposed to establish physician-pharmacist collaborative clinics to manage T2DM in primary hospitals in China. Theoretically, the physician-pharmacist collaborative clinics could alleviate the shortage of medical staff, provide patient education in clinics, reduce patients’ burden of frequent follow ups in tertiary hospitals and decrease patients’ dependence on physicians in primary hospitals, which is especially important in the era of COVID-19 pandemic. This paper reports the development and study procedure of establishing and evaluating physician-pharmacist collaborative clinics to manage T2DM in primary hospitals in Hunan province.

### Aim

This study aims to improve patient’s glucose control and medication adherence, reduce hospitalization or emergency room visits and incidence of complications related to diabetes, and decrease costs on diabetes by implementing physician-pharmacist collaborative clinics in primary hospitals during the COVID-19 pandemic. Moreover, our study will provide experiences to expand the mode of physician-pharmacist collaborative clinics in primary hospitals across China to manage other chronic diseases during and after the COVID-19 pandemic.

## Methods/design

### Study design

The study is a multi-site randomized controlled trial. We will carry out the study in six primary hospitals in Hunan province. Eligible patients will be randomly assigned to the intervention group (physician-pharmacist collaborative clinics) or the control group (usual care clinics led by a physician) and will be followed up at the 3rd, 6th, 9th and 12th month. Comparison between the two groups will be conducted by assessing the clinical parameters, process indicators and costs on diabetes. Fig. 1 describes the study design.

**Fig. 1 Fig1:**
[figure not shown]
Flowchart of the study

### Study participants and inclusion criteria

Patients eligible for this project have to comply with all of the requirements below: have been diagnosed with T2DM; male or female, over the age of 18 years old; the HbA1c level of the past two months was > 7.5% prior to the study and an informed consent signed by the patient or a legal guardian. Patients will be excluded if: pregnancy; have end-stage renal failure (hemodialysis or glomerular filtration rate < 10 mL/min); have dementia or unstable psychiatric conditions; receive treatment for cancer; have congestive heart failure which requires medicine treatment or have a history of acute or chronic pancreatitis. All eligible patients who agree to participate the study have to sign the informed consent form before being enrolled.

Pharmacists eligible for this project have to comply with all of the requirements below: have worked as a clinical pharmacist at the selected primary hospital for over 2 years, with priority given to those with diabetes management experience; have received a standardized training as a clinical pharmacist before this project, with priority given to those in endocrinology specialty; be able to get comprehensive training in the Second Xiangya Hospital for three months and can complete the project.

### Study settings

Currently in Hunan province, county hospitals, township health centers, and village clinics are the major primary health care providers in rural areas. As there are limited pharmacists and their main responsibility is dispensing in village clinics and township health centers, we chose county hospitals as the research sites. Since there are several county hospitals in each county, we selected the best one in that county as our studied primary hospital with the aim of homogenizing the quality of the settings. We divided these counties into three subgroups based on their per capita income levels, namely high, medium and low incomes counties. We sent invitation letters to 27 primary hospitals and 18 agreed to participated in the study. Finally, we randomly selected six of them (two in each subgroup) to conduct the study as shown in Fig. 2.

**Fig. 2 Fig2:**
[figure not shown]
Flow-chart of setting selection and number of patients in the project

### Procedures

#### Training pharmacists and data collectors

Three pharmacists from the primary hospitals assigned to the intervention group will be trained for three months in the Second Xiangya Hospital. The training courses mainly include two aspects, namely diabetes management and cooperative skills, as shown in Table 1. These pharmacists are required to spend most of their training time either in the outpatient clinic of endocrinology or in the wards of endocrinology to get as much experience as possible. Besides the traditional teaching methods, problem-based learning and scenario simulation learning methods will be implemented to train the pharmacists. Serial tests will be carried out to examine how well the knowledge and skills they have mastered.

**Table 1 Tab1:** Training courses for pharmacists from primary hospitals

Training courses	Details	time
Diabetes management	1.Theoretical knowledge □ Basic knowledge of diabetes, including identification of diabetes complications □ Basic knowledge of hypoglycemic a gents(oral & injection medicine) □ treatment target of blood glucose level □ Laboratory tests interpretation □ Medication adherence □ Diet □ Exercise □ lifestyle 2. Practice and Application in patients 3. Six tests to assess their theoretical knowledge and practice skills	Two months
Cooperative skills	1. Theoretical knowledge on communication skills 2. Practice in outpatient clinics and inpatient wards	One month

Six nurses from each of the primary hospitals will be enrolled as data collectors and will be trained for two weeks in the Second Xiangya Hospital. They will be simply introduced about the background of the project, namely diabetes management and pharmacotherapy. These data collectors will get detailed training of patient enrollment talk, informed consent signature and data collection for assessments. Data collectors will be trained to finish both the printed and the electronic CRF (case report form) forms for assessments.

#### Recruitment and withdrawn

At the stage of patient enrollment in each clinic, a trained data collector will stay in the clinic and prepare to talk to patients. Once the physician identifies a potential eligible patient with T2DM in the clinic and simply introduces the project to him/her, the trained data collector will explain the project in details. If the patient agrees to join in the project, the trained data collector will ask the patient to sign the informed consent, and help him/her to fill out the printed CRF form as baseline assessment.

Patients enrolled will be withdrawn from the project if any of the conditions occurs: the patient decides not to continue in the project for any reason; the patient is lost for follow-up for at least twice; the researcher considers the patient is no longer physically and/or psychologically fit to remain in the study. The reasons for withdrawn will be recorded.

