#### Randomization and allocation concealment

The randomization protocol was used to select six out of 18 primary hospitals in Hunan province to carry out the study by using a standard protocol available in the website (http://stattrek.com/statistics/random-number-generator.aspx). There will be three centers in each group (intervention group and control group).

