### Intervention protocol

#### Physician-pharmacist collaborative diabetes clinics

Three physician-pharmacist collaborative diabetes clinics will be established after the pharmacists get comprehensive training. Pharmacists in the collaborative clinics will provide several services which mainly consist of four aspects, including diabetes education, medication guidance, lifestyle intervention, and identification and treatment of adverse drug reaction and complications, as shown in Table 2.

Three measures will be taken to make sure that the project will be carried out smoothly in the collaborative clinics. 1) In the first week, a pharmacist from the Second Xiangya Hospital will stay in the collaborative clinic, monitor the trained local pharmacist and data collector’s work, and give him/her guidance to run the collaborative clinic well. 2) A pharmacist from the Second Xiangya Hospital will periodically go to the primary hospitals and check the progress of the project. Every week, there will be an internet meeting consisting of the PI, main participants and the pharmacists from the intervention group to report the process of the project, describe the problems they meet and exchange their experience in the collaborative clinics. 3) Data collectors are required to entry and upload the electronic CRF forms to the Second Xiangya Hospital within two days when they have finished the printed forms. A separate research staff will carefully check the data and immediately inform the data collectors to amend the errors once occur.

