#### Usual care clinics

Similar to physicians in the collaborative clinics, physicians in the usual care clinics will provide routine services, mainly including diagnosis and treatment without education due to limited time. No pharmacists will be involved in the control group. Data collectors will present in the clinic to enroll patients and collect data of the assessments the same as in the collaborative clinics.

In order to ensure the implementation of the project in the usual care clinics, three measures will be taken: 1) In the first week, a pharmacist from the Second Xiangya Hospital will stay in the clinic and monitor the data collector’s work. A participant from the Second Xiangya Hospital will periodically go to the primary hospitals and check the progress of the project. 2) Every two weeks, an internet meeting consisting of the PI, main participants and the data collectors will be held to monitor the process of the project. 3) Same as the intervention group, data collectors are required to entry and upload the electronic CRF forms to the Second Xiangya Hospital within two days.

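### Hospitals, not patients, are allocated, and patients are recruited openly once the arm is known, so who is invited and who consents can differ between arms despite the stated patient-level randomisation.

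*Protocol article*

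**What the plan says.** The protocol article describes allocation in two ways.

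- **Patients.** Study design: "Eligible patients will be randomly assigned to the intervention group (physician-pharmacist collaborative clinics) or the control group".
- **Hospitals.** Randomization and allocation concealment: "The randomization protocol was used to select six out of 18 primary hospitals in Hunan province to carry out the study", followed by "There will be three centers in each group (intervention group and control group". The section gives no patient-level sequence and no concealment step.

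Two sections give the order of events. Under Training pharmacists and data collectors: "Three pharmacists from the primary hospitals assigned to the intervention group will be trained for three months". Under Physician-pharmacist collaborative diabetes clinics: "Three physician-pharmacist collaborative diabetes clinics will be established after the pharmacists get comprehensive training".

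Recruitment and withdrawn describes enrolment in each clinic. It begins "Once the physician identifies a potential eligible patient with T2DM in the clinic and simply introduces the project to him/her"; the collector then explains the project in detail, and if the patient agrees, "the trained data collector will ask the patient to sign the informed consent". For the control hospitals, Usual care clinics says "Data collectors will present in the clinic to enroll patients and collect data of the assessments the same as in the collaborative clinics", and that no pharmacist takes part.

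Several provisions work in the plan's favour:

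- an HbA1c entry threshold of more than 7.5% (Study participants and inclusion criteria);
- collectors trained in the enrolment talk, with only a simple introduction to the background (Training pharmacists and data collectors);
- standard enrolment procedures (Quality control procedures);
- primary and secondary outcomes adjusted for their baseline values (Outcomes).

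**The concern.** When patients are randomised one by one with concealment, nobody who invites or consents a patient knows the arm, so selection at entry cannot differ systematically between arms. When hospitals are allocated first and patients recruited afterwards by staff who can see the arm, that protection is lost. What is on offer differs: added pharmacist care at three hospitals, usual care at the other three. Which patients the physician mentions the project to, and which agree, may differ accordingly, for example in motivation or willingness to change habits. Those traits bear on adherence, lifestyle, costs and HbA1c at 12 months.

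A reader who relies on Study design would assume the usual protection and attribute the whole difference between arms to the intervention. The limitations in the Discussion name only geography and length of follow-up.

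**Working it through.** **1. The plan's own figure.** Inputs from Sample size determination: difference 0.76, SD 1.0, two-sided α = 0.05, power 90%.

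n per group = 2 × SD² × (z₀.₉₇₅ + z₀.₉₀)² / difference² = 2 × 1.0² × (1.960 + 1.282)² / 0.76² = 21.02 / 0.5776 = 36.4, rounded up to 37. The plan states 36, at which power is 89.7%. With 10% dropout, 36 / 0.9 = 40, as stated. The figure reproduces. It is a formula for independently sampled patients and has no bearing on selection at entry.

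**2. When the arm becomes known.**

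| Step | Section | What it fixes |
|---|---|---|
| Six hospitals chosen, three per group | Randomization and allocation concealment | Arm belongs to the hospital |
| Pharmacists from intervention hospitals trained for three months | Training pharmacists and data collectors | Arm settled before training |
| Collaborative clinics open after training | Physician-pharmacist collaborative diabetes clinics | Arm visible on site |
| Physician identifies patients; collector in the clinic takes consent | Recruitment and withdrawn; Usual care clinics | Recruiters work inside the arm |

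Two links are inferred. The article never uses the words blinded or unblinded; that recruiters know the arm follows from their working in a clinic with or without a pharmacist. That enrolment follows the opening of the collaborative clinics is inferred from enrolment being placed in each clinic.

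**3. Size of a possible shift.** The documents give no figure, so this is an assumption. Let p_I and p_C be the proportions of enrolees in the intervention and control arms who would improve by d HbA1c points more whatever their care. The spurious difference is (p_I − p_C) × d. Take d = 0.5.

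- p_I = p_C: 0.
- p_I = 0.20, p_C = 0: 0.20 × 0.5 = 0.10, and 0.10 / 0.76 = 13% of the target effect.
- p_I = 0.30, p_C = 0: 0.30 × 0.5 = 0.15, and 0.15 / 0.76 = 20%.
- p_I = 0.20, p_C = 0.30: −0.05, against the intervention.

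These are shifts before baseline adjustment, which would remove the part reflected in the baseline value.

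**4. Effect on a test, as an illustration.** Assume no true effect, 300 patients per arm (three hospitals × 100), SD 1.0 and a patient-level two-sided test at 0.05. The standard error is √(2/300) = 0.0816. The probability of a significant result is 1 − Φ(1.96 − b/0.0816) + Φ(−1.96 − b/0.0816), where b is the residual shift.

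| Residual shift b | Probability of P < 0.05 |
|---|---|
| 0 | 5% |
| 0.10 | 23% |
| 0.15 | 45% |
| 0.20 | 69% |
| 0.30 | 96% |

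This test ignores clustering by hospital. The table shows only that, with 300 per arm, a small residual shift can produce a significant result.

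**The case against.** Several counter-arguments stand.

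- **No steering between arms.** A reader might infer that physicians can send motivated patients to the collaborative clinic. They cannot: each hospital has one arm, and Study settings takes one hospital per county. A physician can only invite or not invite. Bias arises only if invitation or consent differs between arms.
- **Partly standardised enrolment.** The trained enrolment talk, standard procedures and like-for-like role of the control-arm collectors reduce differences in how the project is presented. They do not hide the arm or change what is being offered.
- **Baseline adjustment is planned.** The primary outcome is already adjusted for its baseline value, and the Covariates section lists age, gender and education as collected. Imbalance in baseline HbA1c is thus largely dealt with; unmeasured motivation is not.
- **No sourced magnitude.** The 0.10–0.15 range assumes no such selection among control patients, who are volunteers too.
- **Enrolment beyond 100 per hospital is not evidence of selection.** A fixed recruitment window may leave less room for picking patients than a quota.
- **Six clusters are not the cause.** Differential recruitment is systematic, and more hospitals would not balance it.
- **Article format.** Screening logs and consecutive-enrolment rules may sit in the full protocol, so their absence is not an error. The point does not rest on it: the patient-level claim, the hospital-level allocation and the recruitment route are all stated, and the first conflicts with the other two.

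**Conclusion.** The point holds as a misdescription of the design that carries a real risk of bias. The Study design wording is incompatible with hospital-level allocation, and the section on concealment describes none. Patients are recruited after the arm is settled, by staff who can see it, so patient-level randomisation cannot be relied on to protect the comparison.

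The size is unknown. It is zero if selection is equal in both arms, 0.10–0.15 HbA1c points under the assumptions shown, and could run in either direction.

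Two stronger readings are tempting. One is that the arms do differ through selection: the documents show that they can, not that they do. The other is that hospitals were put into arms without randomisation: the text says that six were selected at random and that each group has three, does not say how the arms were assigned, and the figure on site selection is not shown. Neither reading is supported.

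**What to change.** 1. Reword Study design and Randomization and allocation concealment to say that hospitals are allocated, three per arm, and that patients are recruited afterwards without concealment of the arm. Add this to the limitations in the Discussion. This costs a few sentences.
2. Pre-specify that the primary analysis adjusts for age, sex and education as well as the planned baseline HbA1c. All are already collected. This reduces bias from measured imbalance but will not remove bias from unmeasured motivation.
3. Report baseline characteristics by hospital and arm, so that readers can see any imbalance at the level where it would arise.
4. For any recruitment still open, approach consecutive eligible patients with the same script in both arms, and have the collector already in the clinic keep a screening log (age, sex, HbA1c; enrolled, refused or not approached). This is minor extra work per clinic day.
5. For recruitment already closed, report whatever counts of approached and refused patients exist, by hospital. This may be all that is possible: recruitment began in May 2021 with a window of six months, or seven at most, so on plan it ended by about December 2021, before publication in March 2022.

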#### Follow-up visits and data collection

All the patients in either the intervention group or in the control group are required to visit their corresponding clinic at the 3rd, 6th, 9th and 12th month. They are allowed to arrive at the clinic within seven days before or after the appointed day. The measurement domains required to collect, survey methods and collection time-points are listed in Table 3.

**Table 3 Tab3:** Measurement domains, survey methods and collection time-points

Variable	Component	Measurement methods	Baseline	3rd M	6th M	9th M	12th M
**Socio-demographic parameters**	Gender, age, telephone, address, education, occupation and annual income	Face-to-face interview	√				
**Clinical parameters**	Height, weight, waist to hip ratio, fasting blood glucose, 2-h postprandial blood glucose, HbA1c, diabetes complications, blood pressure and lipid files	Face-to-face interview, telephone or online interview	√	√	√	√	√
**Behavior parameters**	Medication adherence, diabetes’ knowledge, lifestyle, diabetes treatment target and treatment behavior		√ √	√	√	√	√ √
	Treatment satisfaction						√
**Economic parameters**	Direct costs (Average daily Medicine, outpatient clinic visit fees, and hospitalization fees if occurs), Indirect costs (deducted income due to absence of working, traffic and accommodation fees)	Face-to-face interview, telephone or online interview	√	√	√	√	√

In order to enhance patients’ follow-up rate, two measures will be taken: 1) The trained data collectors will send a text message to remind the patient three days before the appointed follow-up day. If the patient has not shown up in the clinic one day after the appointed follow-up day, they will call the patient. If the patient still insists not coming, the reasons will be recorded in the CRF form. 2) All the patients from either the control group or the intervention group will receive free tests of fasting blood glucose (FBS), 2-h postprandial blood glucose (2hPBG) and HbA1c at the 3rd, 6th, 9th and 12th month to sustain their involvement in the study.

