#### Secondary outcomes measures

Secondary outcomes are the following measures adjusted for baseline values:patients’ medication adherence, diabetes knowledge and lifestyle;patients’ hospitalization or emergency room visits and incidence of complications related to diabetes;height, weight, waist to hip ratio, blood pressure and lipid files;costs on diabetes management.

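### Unfit patients are withdrawn from the whole project with no outcome follow-up stated, which can lose outcomes selectively in sicker patients and unequally between arms

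*Protocol article*

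**What the plan says.** All references are to the protocol article.

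- **Recruitment and withdrawn.** The rule is mandatory and covers the project, not only the clinic service: "Patients enrolled will be withdrawn from the project if any of the conditions occurs". One condition is that "the patient is lost for follow-up for at least twice". Another is that "the researcher considers the patient is no longer physically and/or psychologically fit to remain in the study". No criterion for fitness is given. The one follow-on action is "The reasons for withdrawn will be recorded".
- **Follow-up visits and data collection.** A patient who does not appear is telephoned. "If the patient still insists not coming, the reasons will be recorded in the CRF form". Table 3 in the same section gives the collection method for the clinical row (which includes complications and HbA1c) and the economic row (which includes hospitalization fees) as "Face-to-face interview, telephone or online interview", at baseline and at months 3, 6, 9 and 12.
- **Secondary outcomes measures.** These include "patients’ hospitalization or emergency room visits and incidence of complications related to diabetes" and the costs of managing diabetes. The Aim section makes reducing all of these a purpose of the trial.
- **Primary outcomes measure.** Glucose control at 12 months.
- **Data analyses.** Mixed models and survival analysis for follow-up data; QALYs from EQ-5D-3L and an ICER over 12 months.
- **Randomization and allocation concealment.** Three centres in each group.

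**The concern.** Whether a patient is physically fit to remain is not independent of the outcomes. An admission or a serious complication is a plausible reason for judging someone unfit, and such patients are also more likely to have further admissions and high costs. A rule that ends participation on that ground makes missingness depend on the outcome.

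The arms may also be affected differently. With three hospitals per group, a site's habit of withdrawing patients readily or reluctantly falls wholly on one arm. Contact differs too. Intervention pharmacists help identify complications, can be called in an emergency (Table 2) and join a weekly project meeting. Control clinics have no pharmacist and meet every two weeks. Illness may therefore be noticed, and acted on, at different rates.

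At stake are the comparisons of admissions, complications and costs, the QALYs and ICER, and to a lesser degree the 12-month glucose values. The arms differ in pharmacist services added to physician care, so nothing in the design requires recording to stop when a patient becomes ill.

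**Working it through.** **1. The plan's own attrition figure.** The only one is the 10% dropout allowance in Sample size determination. The base figure reproduces closely: n = 2 × (1.960 + 1.282)² × 1.0² / 0.76² = 36.4 per group, against 36 stated. With the allowance, 36 / 0.90 = 40, as stated. The sample size is not in question here. The 10% is not split by cause or by arm.

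**2. Does each hospital run one arm?** The Study design section speaks of patients being assigned. The randomization section puts three centres in each group, and the training section refers to hospitals assigned to the intervention group. On that reading, staff know the arm. The article describes no blinding.

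**3. Does the telephone route rescue a withdrawn patient?** Table 3 provides remote collection for patients in follow-up. The withdrawal rule ends participation in the project, and nothing says that remote collection continues after it.

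**4. How much could it matter?** The documents give no admission or withdrawal rates, so this is an illustration only. Assumptions:

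- 300 patients per arm (3 hospitals × 100).
- True 12-month admission risk p of 15% in control and 10% in intervention, a difference of 5.0 points.
- A share w of admitted patients is withdrawn before the admission is recorded.
- 5% of non-admitted patients are withdrawn.
- Only the remaining patients are analysed.

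Observed risk = p(1 − w) / [p(1 − w) + (1 − p) × 0.95].

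| w control | w intervention | Observed control | Observed intervention | Difference (points) |
|---|---|---|---|---|
| 10% | 10% | 14.3% | 9.5% | 4.8 |
| 25% | 25% | 12.2% | 8.1% | 4.2 |
| 50% | 50% | 8.5% | 5.5% | 3.0 |
| 50% | 10% | 8.5% | 9.5% | -1.0 |
| 10% | 50% | 14.3% | 5.5% | 8.8 |

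Worked example, fourth row. Control: 0.075 / (0.075 + 0.8075) = 8.5%. Intervention: 0.090 / (0.090 + 0.855) = 9.5%.

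**5. Is that outside the planned dropout?** In the fourth row, control loses 0.50 × 45 + 0.05 × 255 = 35.25 patients and intervention loses 0.10 × 30 + 0.05 × 270 = 16.5. Together that is 51.75 / 600 = 8.6%. In the fifth row the losses are 17.25 and 28.5, or 45.75 / 600 = 7.6%. Both lie within 10%. An allowance for numbers gives no protection against selective loss.

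**6. Costs, as a ceiling.** Assume 3% of an arm is withdrawn as unfit and costs 10 times the ordinary patient. The true mean is 0.97 × 1 + 0.03 × 10 = 1.27. If those patients vanish altogether the observed mean is 1.00, an understatement of 1 − 1/1.27 = 21%. Costs are collected quarterly, so total loss is unlikely. If half of their cost was already recorded and is kept, the sum is 0.97 + 0.03 × 5 = 1.12, an understatement of 1 − 1.12/1.27 = 12%.

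**The case against.** Several counter-arguments carry weight.

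- **A condensed article.** Handling of data after withdrawal is often left to a full protocol or SAP. That excuses silence on analysis. It does not excuse the stated rule, which is mandatory, reaches the whole project and sits in the text shown. The full protocol may nevertheless separate stopping attendance from stopping data collection.
- **The reason is recorded.** If an admission prompts the withdrawal, the recorded reason may capture it. Counted as an event in a survival analysis, it would not be censored at that moment. This stands, and it narrows the likely loss to later events, fee detail, later costs, EQ-5D and 12-month glucose. The table above, which assumes that the admission itself goes unrecorded, is therefore towards the severe end.
- **Earlier data survive.** Nothing says that data recorded before withdrawal are deleted, and mixed models can use earlier visits. This also stands. Those models are protected only if withdrawal is explained by what has been recorded, which an undefined fitness judgement does not ensure.

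A reader might infer that outcomes are lost in exactly the patients who have them. The documents do not say so: an admitted patient is not automatically withdrawn, and the ground also covers psychological unfitness. A reader might also infer that the no-show call serves only to note a reason. The text mentions only reasons, and does so for a patient who refuses to come. Table 3 allows remote collection, so it is unclear whether outcomes are asked on that call. Nor does one missed visit withdraw anyone; the rule requires at least two losses to follow-up.

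**Conclusion.** The point holds in a limited form. The rule ends participation on a discretionary, health-related ground, judged by staff who can be taken to know the arm, with no outcome collection stated afterwards. It can lose information disproportionately in sicker patients and unequally between arms. The documents fix neither the size nor the direction. On the assumptions shown, the effect on a 5.0-point difference runs from slight (4.8 points at 10% loss in both arms) to a reversal (-1.0) or an exaggeration (8.8) when loss is unequal.

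The documents do not support the stronger conclusion that admissions and costs will be calculated only on patients who stayed well. The exposure is mainly in secondary and economic outcomes, with the 12-month glucose values also open to loss. This is a cheap improvement that should be made, held with medium confidence because the full protocol is not shown.

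**What to change.** **Recruitment and withdrawn.** Separate the end of clinic attendance or pharmacist sessions from the end of outcome collection. A patient judged unfit may cease the former but stays in outcome follow-up at months 3, 6, 9 and 12 unless consent is withdrawn. Take admissions, emergency visits, complications, death, costs and EQ-5D by the telephone or online route in Table 3, with guardian report where needed (the Baseline interview section already accepts it for costs). Name EQ-5D, emergency visits and death explicitly, since Table 3 does not list them. Obtain HbA1c where possible. Analyse these patients in their assigned arm. This concerns data collection only and takes no position on when a patient should stop attending.

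**Follow-up visits and data collection.** Reconcile the no-show call with Table 3 by having the call also ask the hospitalisation, complication and cost items.

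**Cost.** A few sentences, added questions in a call already planned, and continued contact with a probably small number of patients. Some data will come from telephone or guardian report rather than a clinic visit, and HbA1c will still be missing for some.
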